#### Risk categorisation and returning risk assessment results.

Based on the CanRisk breast cancer risk estimate and current NICE guidelines [7], participants are categorised into one of three risk groups: near population level risk, near population level risk but with additional features in the family history (i.e., sarcoma in relative < 45 years; glioma or childhood adrenal cortical carcinomas; complicated patterns of multiple cancers at a young age; Jewish ancestry), and moderate or high risk.

Women with an estimated breast cancer risk in the near population level risk group and without any additional risk factors based on their family history (see Table 1) receive a letter from the study team informing them that they are at near population level risk for breast cancer along with a breast awareness leaflet and the risk output from the CanRisk tool. The breast awareness leaflet is in line with current NICE guidance covering all the required fields (i.e., 5-point NHS plan for being breast aware, when to examine your breasts, what to look for, changes to look for, lifestyle advice, and further information). A copy of both the letter and risk output is also sent to the participants’ GP. Women with an estimated risk at near population level but with additional risk factors within their family history and those at moderate or high risk receive a results letter informing them that they may be at above average population level risk for breast cancer and advise them to make an appointment to discuss with their GP. They are also sent the breast awareness leaflet, and a copy of both the letter and risk output is sent to the participants’ GP. The GP or a delegate practice staff member adds the appropriate codes to the medical records for all participants.

**Table 1 pone.0336902.t001:** Risk categorisation.

Risk	Near population risk	Moderate risk	High risk
Lifetime risk between ages 20 and 80	<17%	≥17% - < 30%	≥30%
Risk between ages 40 and 50	<3%	≥3% - < 8%	≥8%

Women confirmed to have additional risk factors based on their family history or those at estimated moderate or high risk for breast cancer are offered referral to the regional clinical genetics service using a specially designed referral proforma. Women referred to the regional clinical genetics service are then managed in line with current practice.

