Table 1 shows the risk cut offs for near population risk, moderate risk and high risk for lifetime risk (defined as the risk between the ages of 20 and 80), and 10 year risk between the ages of 40 and 50.[7] For women falling in different categories based on the two definitions of risk, whichever is highest determines the risk category (i.e., near population risk, moderate and high risk) they will be classified as for the purposes of implementing current NICE guideline [7].

A list of women advised to make an appointment with their GP is sent to practices each month. Any women who have not booked a consultation or already consulted with a GP is contacted by practice staff and supported to book an appointment if they wish. Each patient contact and any reasons for not wishing to consult with a GP is recorded by the practice staff.

The process for returning results to participants and subsequent management is shown in Fig 2.

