**Moderators**				
Numeracy [28]	•			
Health literacy [29]	•			
Beliefs about breast cancer [30]	•			
Time orientation [31]	•			
Intolerance of uncertainty [32]	•			

Table 2 specifies all measures, instruments and data collection points (baseline and at 1, 3 and 6 months after receiving the risk assessment results). All outcomes will be measured by self-report and include risk perception, psychological impacts of the risk assessment, lifestyle and behaviour, and actions taken following the risk assessment. Risk perception will be assessed using questions about absolute and comparative risk, risk conviction and recall of risk. Psychological measures include cancer-related worry, anxiety and quality of life using the Lerman cancer worry scale [21], the short-form of the state scale of the Spielberger State Trait Anxiety Inventory (STAI) [22] and the EQ-5D-5L [23, 24] respectively. These have been chosen as the Lerman cancer worry scale and short-form STAI have been widely used in the literature and so will allow comparison with other studies, and the EQ-5D-5L is the recommended measure for use in economic analyses by NICE [25]. We will also collect data on: motivations and concerns regarding participation in the study using multiple choice questions and short open text boxes questions; the acceptability of the study using 5-point Likert scale questions [26]; the impact of cancer risk assessment using the MICRA scale [27]; satisfaction with the test using 5-point Likert scale; questions assessing the degree of satisfaction with the multifactorial cancer risk assessment; views on the risk information using 5-point Likert scale questions assessing the information in the CanRisk report; views on the GP consultation, including assessing the usefulness of the consultation and whether the appointment clarified understanding of breast cancer risk. Additionally, patients who agree to have their appointment recorded will receive an optional survey immediately after their GP consultation exploring their experience of the appointment. Attitudes towards risk management options (i.e., earlier or more frequent screening, medication and surgery) will also be measured via standardised scales and multiple-choice questions reviewed by patient and public partners. Lifestyle and behavioural data will be collected through multiple choice questions; these will include question about current behaviour regarding breast self-examination, intention to attend screening, change in behaviour (i.e., weight, alcohol consumption and exercise) and healthcare utilisation (i.e., number and type of contact) specifically focusing on breast health in the six months prior to baseline and six months after baseline. Data on actions following the risk assessment will only be collected for women found to be at increased risk and if they have attended the GP appointment. Actions measured will include multiple choice questions about the attendance at the GP appointment (or intention if not done) as part of the study and uptake (or intention if not done) of risk reduction strategies (i.e., earlier or more frequent screening, medication and surgery). We will also collect data on numeracy [28], health literacy [29], beliefs about breast cancer [30], time orientation [31], and intolerance of uncertainty [32]. These will be considered as moderators for the measures above that will help test interactions between variables in the study.

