### Analysis

#### Quantitative data analysis.

Descriptive statistics will be used to summarise characteristics of the eligible population and study population at baseline, recruitment and retention rates, satisfaction and understanding of test results and consultations, healthcare utilisation, and intention to change behaviour overall and by risk group. Means and standard deviations will be used for normally distributed continuous variables, medians and interquartile range for non-normally distributed continuous variables, and numbers and percentages for categorical variables. Where reported, all proportions and differences in proportions will be presented with 95% confidence intervals.

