#### Psychological and behavioural impact of multifactorial breast cancer risk assessment.

For continuous outcomes (anxiety, worry, risk perception, recall of risk information, and intentions) analysis of covariance will be used to calculate change at each follow-up within each risk group, adjusting for clustering between each GP practice. Any differences between the risk groups on analysis of covariance will be tested using an F-test, followed by estimation of the comparison between those at near population level risk and those at moderate or high risk based on the CanRisk assessment. All models will be adjusted for age, ethnicity, education level, deprivation, baseline EQ-5D and general practice. The size of the change between groups will be interpreted by comparison with the standard deviation (SD), with the criteria for clinically relevant change being a change of 0.5 SD [29]. We will also test for interactions between the risk groups and age, family history of breast cancer, numeracy, beliefs about breast cancer, time orientation, intolerance of uncertainty and responding “not anxious or depressed” versus “slightly/moderately/severely or extremely anxious or depressed” on EQ-5D at baseline. Analyses will be repeated within the subgroups where the p value for interaction is < 0.05.

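### Recall of risk gets the same change-ANCOVA, F-test and 0.5 SD rule as anxiety, although it has no baseline and no stated scoring against the woman's own result; perceived risk needs an accuracy analysis beside its mean change

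*Protocol article*

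**What the plan says.** The analysis section on psychological and behavioural impact states: "For continuous outcomes (anxiety, worry, risk perception, recall of risk information, and intentions) analysis of covariance will be used". The aim is an estimate of change by risk group at every follow-up. The section continues: "Any differences between the risk groups on analysis of covariance will be tested using an F-test". Next comes a single contrast, near-population women against moderate/high women as classified by CanRisk. The size of the change between groups is judged against the standard deviation, "with the criteria for clinically relevant change being a change of 0.5 SD". That criterion is not restricted to particular outcomes.

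The measures are described under Table 2: "Risk perception will be assessed using questions about absolute and comparative risk, risk conviction and recall of risk". No scoring is given. Table 2 marks absolute and comparative perception and conviction at baseline and at 1, 3 and 6 months. It marks recall of risk information at 1, 3 and 6 months only.

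Table 1 forms the risk categories from two rows. The first is "Lifetime risk between ages 20 and 80", cut at 17% and 30%; the second is risk between ages 40 and 50, cut at 3% and 8%. Where they disagree, "whichever is highest determines the risk category". Each woman receives a letter worded by group.

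The general quantitative analysis section also promises a descriptive summary of "satisfaction and understanding of test results and consultations", overall and by risk group. The article nowhere states that a woman's recalled or perceived risk is compared with the risk in her own report.

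**The concern.** Anxiety and worry have no value that a woman ought to report given her risk group, so a group difference in them is informative in itself. Recall is different. The grouping variable is derived from the information that women are asked to recall, so on a raw scale the groups should differ if the letters worked. A significant F-test would then be compatible with good recall, partial recall or systematic exaggeration.

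Perceived absolute risk raises a narrower issue. After an informative result, over-estimators should come down and under-estimators should go up, so mean change can be near zero although every woman has become more accurate. A 0.5 SD difference between groups may be no more than the intended effect of telling women their risk, yet the plan's criterion would label it clinically relevant.

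At stake is what the feasibility study can tell a future trial about returning results by letter: how many women can state their result correctly at 1, 3 and 6 months, and whether their perceived risk has moved towards it.

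**Working it through.** **1. The plan's own 0.5 SD figure.** The sample size section claims 90% power for a 0.5 SD change in anxiety or worry after 40% loss, with 170 of 1,000 women above population risk. Retained: 170 × 0.6 = 102 and 830 × 0.6 = 498.
- Within the moderate/high group (one-sample t, two-sided 0.05), power is 99.9% if 0.5 is in SDs of the change. It is 94% if baseline and follow-up are uncorrelated (0.5/√2 = 0.354 SD of the change).
- Between groups, SE = √(1/102 + 1/498) = 0.1087 SD, and 0.5/0.1087 = 4.60, giving 99.6%.

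The 90% claim holds as a floor. It is made for anxiety or worry only, and the present point does not depend on it.

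**2. Baseline.** The ANCOVA is planned to give change, with recall in the list. Table 2 has no baseline recall, and none is possible before a result has been issued. Change from baseline in recall is therefore undefined on any scoring.

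**3. If recall is the recalled lifetime percentage.** Assumptions, none of them in the article: log-normal lifetime risk with P(risk ≥ 17%) = 0.17; median m of 10% to 12%; groups split on lifetime risk alone; two groups. Then σ = ln(17/m)/0.954.

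| Median | Mean below 17% | Mean at or above 17% | Difference (points) | Within-group SD (points) | Difference in SD |
|---|---|---|---|---|---|
| 10% | 9.2% | 23.7% | 14.5 | 4.4 | 3.3 |
| 11% | 10.2% | 22.2% | 12.0 | 3.7 | 3.2 |
| 12% | 11.2% | 21.0% | 9.8 | 3.1 | 3.1 |

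That is perfect recall. With 102 and 498 women, t = 3.1/0.1087 ≈ 29 or more.

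Now degrade the recall:
- 40% of moderate/high women recall a near-population figure: the mean difference falls to 0.6 of its value (0.6 × 14.5 = 8.7 points at a median of 10%). The standardised difference is 1.6 to 1.7 SD.
- The same, plus reporting error with SD 10 points: 0.55 to 0.78 SD, t = 0.55/0.1087 ≈ 5 or more.
- No mis-recall, but unbiased error with SD 20 points: 0.48 to 0.71 SD (at a median of 10%, 14.5/√(4.4² + 20²) = 0.71). The test rejects in 99% to 100% of simulated studies of 600 women.
- Every woman doubles her risk, error SD 20 points (median 10%): rejects in 100%.
- Recall unrelated to the result: rejects in 5%.

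The second and third settings describe different recall failures and give nearly the same group difference, so the statistic does not identify how good recall is. With a median of 12% and error SD of 20 points the difference falls just under 0.5 SD, so the threshold is not crossed in every setting.

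**4. If recall is scored for accuracy.** Using recalled minus communicated risk, with equal accuracy in both groups, the test rejects in about 4% to 6%. Scored correct/incorrect at 70% in both groups, it rejects in 5%. The F-test then behaves as it should, so everything in step 3 turns on the unstated scoring.

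**5. Perceived absolute risk.** If two women with the same CanRisk estimate start d points above and d points below it, and both become accurate, their changes are −d and +d. Mean change is 0, while mean absolute error falls from d to 0. Only a comparison with the woman's own estimate shows this.

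**The case against.** The strongest reply is that raw scoring is an inference. A reader might take the word continuous to mean that women's stated percentages go straight into the model, but the article does not say so. An accuracy score can also be continuous, and item scoring is commonly left to a full protocol or analysis plan that is not shown here. This stands, and it makes the recall simulation conditional. It does not answer the missing baseline, nor the use of 0.5 SD as a mark of clinical relevance for recall.

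Other stronger readings are also unsupported:
- A reader might infer that the test rejects whether or not women remember. It does not: it rejects in about 5% when recall is unrelated to the result.
- A reader might infer that the groups are told different risks by definition. The category is the higher of two scales, so groups can overlap on either one. Near-population women with family history features also get the same letter message as moderate/high women.
- A reader might infer that the between-group comparison of perceived risk is invalid. It is a legitimate measure of impact: perception has a baseline, and movement is not guaranteed.
- A reader might infer that the study cannot report correct recall. The F-test is not offered as a test of understanding, and the descriptive summary of understanding could include it. However, Table 2 lists no measure under that name, and the article does not tie the summary to each woman's own result.

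Recall is not a progression criterion, which limits the weight of the point.

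**Conclusion.** The point stands in limited form. The change analysis cannot be carried out for recall as Table 2 schedules it. If recall is the recalled risk value, the F-test between risk groups does not measure how well women recall their result. The expected difference is about 3 SD under perfect recall and 1.6 to 1.7 SD with 40% mis-recall in the moderate/high group, given the assumed log-normal distribution, a median of 10% to 12% and a split on lifetime risk alone. If recall is an accuracy score, that part of the objection falls away.

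For perceived absolute risk the planned comparison can stay. It is incomplete, because a mean can conceal opposite movements, and a 0.5 SD difference there is not in itself a sign of harm or benefit. The sample size section uses 0.5 SD only for anxiety and worry. This should be corrected before analysis, but it does not threaten the study's main feasibility estimates.

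**What to change.** In the section on psychological and behavioural impact:
- Take recall out of the change-ANCOVA. Score it against the category and figure communicated in the woman's own letter and report, and give the proportion correct with 95% CI by risk group at 1, 3 and 6 months. State the reference for near-population women with family history features, whose letter message and CanRisk category differ.
- Keep the ANCOVA for perceived risk. Add accuracy of perceived absolute risk against the woman's CanRisk estimate over the same time horizon: over-, under- and accurate estimation by risk group and time point, with the band for accurate fixed in advance.
- Limit the 0.5 SD clinical-relevance criterion to anxiety and worry.

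Precision is adequate. If 70% were correct (an assumption), the 95% CI would be ±1.96√(0.7 × 0.3/102) = ±8.9 points in the moderate/high group and ±1.96√(0.7 × 0.3/498) = ±4.0 points in the rest. The study team generates each woman's estimate, so the cost is wording, derived variables and a small amount of extra analysis, with no new data.

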## Study outcomes and measures

The study aims to generate data on the following outcomes:

Uptake of multifactorial breast cancer risk assessment, including the proportion of those invited who consent and the proportion of those invited who complete the breast cancer risk assessment, with or without the inclusion of the polygenic risk score.Distribution of breast cancer risk, including the proportion of women who consent who are at moderate or high risk on the initial CanRisk assessment in general practice (with or without the PGS) and those at moderate or high-risk following assessment in secondary/tertiary care.Proportion of women at moderate or high risk of breast cancer. The proportion of registered women aged 40–48 years at the start of the study at participating practices who are at moderate or high risk of breast cancer after assessment in secondary/tertiary care will be compared with the proportion of women aged 40–48 years at moderate or high risk of breast cancer after referral to secondary/tertiary care at non-participating practices across Cambridgeshire and Peterborough during the same time period, and also compared with the proportion of registered women aged 40–48 years at participating practices in the 12 months prior to the study.Uptake of risk-reducing interventions, including the proportion of those at moderate or high risk who attend for a GP appointment, are referred to secondary/tertiary care, and take up enhanced screening and/or preventative medication.Completeness of risk factor information collected through MyCanRisk, including the presence of information completed for non-family history risk factors (e.g., height, weight, alcohol, women’s health) and the number of family members included in the pedigree.Change in psychological and behaviour measures (Table 2) following multifactorial breast cancer risk assessment at one month, three months, and six months after receiving the risk estimate.Acceptability of the pathway of proactive multifactorial risk assessment within general practice to women and GPs, including response rates and completion of questionnaires and the willingness for practices to take part.Costs and workload associated with delivery of proactive multifactorial risk assessment.

**Table 2 pone.0336902.t002:** Assessments.

Construct	Baseline	1 month	3 months	6 months

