**Outcomes**				
Risk perception				
Breast cancer risk perception (absolute)	•	•	•	•
Breast cancer risk perception (comparative)	•	•	•	•
Breast cancer risk conviction	•	•	•	•
Recall of risk information		•	•	•
Psychological				
Anxiety [22]	•	•	•	•
Cancer-specific worry [21]	•	•	•	•
Quality of life [24]	•	•	•	•
Impact of cancer risk assessment [27]		•	•	•
Satisfaction with test		•		
Views on the risk information [33]		•		
Attitude towards risk management options		•	•	•
Lifestyle and behavioural				
Current behaviour (breast self-examination)	•	•	•	•
Intention to attend screening	•	•	•	•
Change in behaviour (weight, alcohol consumption, exercise)		•	•	•
Healthcare utilisation	•			•
Actions following risk assessment (moderate/high risk or those with additional risk factors)				
Consultation with GP (or intention if not done)		•	•	•
Uptake of risk reduction strategies (or intention if not done)				
Enhanced screening		•	•	•
Risk reducing medication		•	•	•
Surgery		•	•	•
Process evaluation				
Acceptability [26]	•		•	
Motivations and concerns	•			
Views on GP consultation (only for moderate/high risk or those with additional risk factors)		•		

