### Sample size

Based on an uptake of 16% in the only study in the UK that invited women to complete a breast cancer risk assessment [35], we estimate that to recruit 1,000 women we need to invite approximately 5,000 women from across the GP practices.

Based on distributions of known risk factors in the UK, we estimate that approximately 17% (170) of those 1,000 women will be at above population-level risk [1]. This will allow us to estimate:

the proportion of eligible women in each practice who consent to take part in the study with an accuracy of +/- 1.1% (width of the 95% CI) based on an estimate of 20%the proportion of eligible women in each practice who consent who complete the risk assessment with an accuracy of +/- 2.5% based on an estimate of 80%the proportion of women who consent who are at moderate or high risk on initial CanRisk assessment in general practice with an accuracy of +/- 2.5% based on an estimate of 17%the proportion of those at moderate or high risk who attend for an appointment with a GP and who are referred to secondary/tertiary care with an accuracy of +/- 5.7% based on an estimate of 80%

Allowing for a 40% loss to follow-up, 1,000 participants will allow us to detect a change in anxiety or worry of 0.5 SD or greater at each time point at p < 0.05 and 90% power in both women at population level risk and in the subgroup identified at moderate or high risk. 1,000 participants will also allow us to detect an estimated increase in the proportion of registered women identified at moderate and high risk through proactive multifactorial risk assessment across all the participating practices compared with the 12 months prior to the study with a 95% confidence interval of +/- 0.005 (5 per 1,000 registered women).

Together with data on the acceptability of the proactive multifactorial breast cancer risk assessment, the following progression criteria will be evaluated to judge whether a subsequent full trial of proactive multifactorial breast cancer risk assessment would be feasible: 16% uptake into the study; 60% response to follow-up questionnaires; 80% of women receiving their breast cancer risk and offered subsequent risk management advice/referral. If any of those criteria are not met, we will use the data from the process evaluation to adapt the approach for subsequent feasibility and/or pilot studies before consider progressing to a subsequent full trial.

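### The model for psychological change does not name its dependent variable or list the outcome's own baseline as a covariate, and it counts recall, which has no baseline, as a change outcome

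*Protocol article*

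**What the plan says.** In the Analysis section of the protocol article, the paragraph on psychological and behavioural impact sets the method: "For continuous outcomes (anxiety, worry, risk perception, recall of risk information, and intentions) analysis of covariance will be used to calculate change at each follow-up". This is done within each risk group. An F-test across the groups comes next, and then "estimation of the comparison between those at near population level risk and those at moderate or high risk based on the CanRisk assessment". One covariate list serves every model: "All models will be adjusted for age, ethnicity, education level, deprivation, baseline EQ-5D and general practice". A change of 0.5 SD is taken as clinically relevant.

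Under Study outcomes and measures the outcome is defined as "Change in psychological and behaviour measures (Table 2) following multifactorial breast cancer risk assessment at one month, three months, and six months".

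Table 2 shows anxiety, cancer-specific worry, the risk perception items and intention to attend screening at baseline and at 1, 3 and 6 months. The row "Recall of risk information" is marked at 1, 3 and 6 months only.

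**The concern.** The paragraph leaves two things open that decide what the risk-group contrast means: whether the dependent variable is the follow-up score or the change score, and whether the outcome's own baseline is in the model. The list reads as complete, since it covers all models. It also names a baseline covariate, and that covariate is EQ-5D rather than the outcome's own baseline score.

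This matters because the groups are formed by the CanRisk estimate. The section on breast cancer risk assessment says that this estimate uses family history, among other factors. Women often know their family history before they join, so worry and perceived risk may already differ between groups at baseline. A difference at follow-up could then be an old difference carried forward, and a difference in change could be regression to the mean. Either could be read as the effect of receiving the risk result.

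The recall item is a plain conflict between two places. The analysis paragraph asks for change in recall, while Table 2 provides no baseline from which to measure it. A woman cannot recall a risk result before she has been given one.

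**Working it through.** **Inputs from the protocol article.** There are 1,000 participants, of whom 17% (170) are expected above population-level risk (Sample size). The same section plans with these words: "Allowing for a 40% loss to follow-up". That leaves 170 × 0.6 = 102 women at moderate or high risk and 830 × 0.6 = 498 at near-population risk. The relevance criterion is 0.5 SD.

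**Inputs assumed.** The article gives neither the baseline difference between groups (d, in SD units) nor the within-group correlation of baseline with follow-up (r). I take d = 0.2 to 0.4 and r = 0.5 to 0.7, with equal variances and no true effect of the risk result.

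**The plan's own figure.** The article states 90% power for a 0.5 SD change in anxiety or worry within each risk group. With 102 women and two-sided alpha of 0.05, power is Φ(0.5√102 − 1.96) = 99.9% if the SD of change equals the SD of the score. It is Φ(0.5√102/√2 − 1.96) = 94.6% if r = 0. The claim is met as a minimum and is not in dispute.

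**Expected contrast with no true effect.** Two data-generating assumptions are considered.

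| Assumption | Follow-up score, no own baseline | Change score, no own baseline | Own baseline added |
|---|---|---|---|
| Follow-up depends on baseline (regression to the mean) | r·d | −(1−r)·d | 0 |
| Groups would change in parallel | d | 0 | (1−r)·d |

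Under the first assumption:
- Follow-up score: 0.5 × 0.2 = +0.10 to 0.7 × 0.4 = +0.28 SD.
- Change score: −0.3 × 0.2 = −0.06 to −0.5 × 0.4 = −0.20 SD.

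The two possible dependent variables therefore give shifts of opposite sign. With d = 0 every entry in the table is zero.

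**Does EQ-5D stand in for the missing baseline?** A simulation used 600 women, 17% at moderate/high risk, d = 0.3, r = 0.6, EQ-5D correlated 0.4 with the within-group part of the baseline outcome, and 1,000 runs. All models were adjusted for EQ-5D.
- Follow-up depends on baseline: +0.18 SD (follow-up score), −0.12 SD (change score), 0.00 (own baseline added).
- Parallel change: +0.30, about 0.01 and +0.12 SD respectively.

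These match the closed forms. EQ-5D did not remove the shift. In this set-up EQ-5D does not itself differ between groups; if it did, it could absorb part of the imbalance.

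**Precision.** Relative to the variance of the score, the residual variance is 1 for the follow-up score, 2(1−r) for the change score and 1−r² with own baseline.
- Own baseline against follow-up score: 1−r² = 0.75 to 0.51, a reduction of 25% to 49%.
- Own baseline against change score: (1+r)/2 = 0.75 to 0.85, a reduction of 25% to 15%.

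The between-group difference detectable at 90% power is (1.96 + 1.28) × √[v(1/102 + 1/498)], where v is the relative variance. For r = 0.5 to 0.7 this gives 0.35 SD (follow-up score), 0.35 to 0.27 SD (change score) and 0.31 to 0.25 SD (own baseline added).

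**Recall.** The analysis paragraph lists recall among the outcomes for which change is calculated, and Table 2 leaves its baseline cell empty. No arithmetic is needed: the quantity does not exist.

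**The case against.** The best reply is that analysis of covariance of change normally includes the baseline score, so the listed variables may be further adjusters and nothing may have been left out. That is possible, and it is why the point is one of ambiguity as well as omission. It is weakened by the text: the list covers all models, it names a different baseline measure, and the same sentence includes recall, for which own-baseline adjustment cannot be implied.

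A reader might infer that the risk-group contrast is biased. The document does not support that without conditions. Equal baselines give no shift. If the groups would change in parallel, the change score is unbiased and adding the baseline itself moves the contrast, by +0.12 SD at d = 0.3 and r = 0.6. This is Lord's paradox, and it arises precisely because the groups are not randomised. The follow-up-score figures, the larger ones, also belong to the reading that fits the word change least well.

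A reader might also infer that one planned analysis cannot be run at all. Only change from baseline in recall is impossible; recall at each follow-up can be compared between groups with the listed covariates.

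Finally, a reader might take separate models at each follow-up, together with the 40% loss allowed for, as a reason to require a repeated-measures model. Separate models are legitimate, and longitudinal and missing-data methods are commonly left to an analysis plan that is not shown here.

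It is also fair to say that every shift computed over the assumed range lies below 0.5 SD. Power for a 0.5 SD difference between 102 and 498 women is 99.6% without own-baseline adjustment. The progression criteria do not use this contrast.

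**Conclusion.** The point holds in a limited form and is worth correcting. As written, the model leaves its dependent variable unstated and omits the outcome's own baseline from a list that covers all models, so the contrast between risk groups is open to distortion from baseline imbalance. The size is +0.10 to +0.28 SD or −0.06 to −0.20 SD, according to which score is modelled. It rests on assumed values of d and r, on no true effect, and on follow-up depending on baseline. The loss of precision rests on the assumed r and does not threaten the stated power. Imbalance between the risk groups does not affect the estimate of change within each group.

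The statement on recall is wrong as it stands and needs no assumption: change from baseline in recall cannot be calculated from the data in Table 2.

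**What to change.** - State for each outcome whether the follow-up score or the change score is the dependent variable.
- Add the outcome's own baseline score as a covariate wherever Table 2 collects it, alongside the existing list.
- Report a change-score analysis without own-baseline adjustment as a sensitivity analysis, and say in advance that the two can differ because the groups are not randomised.
- Take recall out of the change analysis and compare it between risk groups at 1, 3 and 6 months.

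The cost is a change of wording and one additional analysis per outcome. Every variable needed is already collected. The small downside is that the primary and sensitivity results may disagree and will then need interpretation. A repeated-measures model is optional and is not part of this point.
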